### Randomization

Randomization will be performed by an independent statistician by generating allocation numbers using a randomization allocation program. The participants will not be stratified. They will randomly be assigned into KRG and placebo groups at a 1:1 ratio. The investigator will be subsequently notified of the number assigned to each participant and the participants will be given a random number at their second visit. The allocation table of participants will be kept by an independent statistician until the end of the study.

### Blinding

The patients will be blinded to the treatment that they are provided. The investigator and clinical pharmacist will be also blinded to the randomization. Only the independent statistician will be aware of the randomization.

### Ethical approval

The protocol of this trial has been approved by the institutional review board (IRB) and the ethics committee of Kyung Hee University Hospital at Gangdong, Seoul, Korea. The permission number of this study is KHNMC-OH-IRB 2012–004 and the protocol identification number on ClinicalTrials.gov is NCT01664156. Written informed consent will be obtained from all participants prior to enrollment, and patients will be given adequate time to declare if they wish to participate before signing the consent form.

### Recruitment

Information will be sent by short message service (SMS) to patients with CHHF who were previously identified at the Kyung Hee University Hospital at Gangdong. Public advertisements will be placed in the newspaper and homepage of the hospital to recruit participants. Posters, brochures and banners will be placed inside the hospital.

### Concomitant therapy

During the clinical trial, patients will be prohibited from taking any kind of drugs or therapies that might affect symptoms related to CHHF. These include herbal medicines, acupuncture, moxibustion, cupping and infrared treatment. Furthermore, the patients will be prohibited from taking hypertensive or diabetic medications and thrombolytic agents that affect vascular or endothelial functions. However, the patients will be permitted to take medications that would not affect CHHF. For example, medications for a common cold, stomachache, diarrhea and menstrual pain will be allowed.

### Statistical analysis

An independent statistician will perform the statistical analyses of all data in a blinded manner. An efficacy analysis will be performed for both ITT (intention-to-treat) and PP (per-protocol) data set. Baseline characteristics such as age and body mass index (BMI) between the two groups will be compared using independent *t*-test or chi square test. The target variables for analysis in this study include the following: (1) change of skin temperature and VAS scores of cold hypersensitivity in the hands; (2) change of skin temperature and VAS scores of cold hypersensitivity in the feet; (3) RR of the skin temperature by the CST of the hands; (4) the DDD of the hands; (5) power variables of HRV; and (6) the SF-36. All values will be presented as mean ± SD. The paired *t*-test will be used to compare data between the baseline (visit 2) and after the treatment (visit 4) in each group. Comparison between the two groups will be performed using independent *t*-test at each time. If there are significant differences between the two groups at the baseline, we will compare the variables using ANCOVA. All statistical analyses of data will be performed by using SPSS version 17.0 (SPSS Inc., Chicago, IL), with *P*- values <0.05 representing statistical significance.

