HRV is used to study the activity of the autonomic nervous system indirectly. Low-frequency (LF) power is thought to be strongly related to sympathetic nerve system activity and correlates with the regulation of blood pressure and peripheral vascular tone. High-frequency (HF) power reflects sinus arrhythmia and breathing activity and is strongly based on parasympathetic nerve system activity [20]. The ratio of LF to HF power is commonly interpreted as an indicator of the relative balance between sympathetic and parasympathetic activity, with higher ratios corresponding to higher relative sympathetic activity [21]. The total power is not a specific indicator of a particular type of autonomic nervous system expression, but is rather an indicator of the total amount of variability, which includes all of the different possible influences on heart rate variation [20].

CHHF may lower quality of life by interfering with daily life and restricting activities in the cold environment. Therefore, improving quality of life is another important goal in the treatment of CHHF. The SF-36 is a generic instrument to measure health-related quality of life and is widely used to survey physical and emotional health. The validated Korean version of SF-36 that will be used in this study was provided by the Health Assessment Laboratory (Boston, MA, USA). It consists of 36 questions grouped into eight dimensions: physical function (10 items), role limitations owing to physical health problems (4 items), bodily pain (2 items), general health perception (6 items), energy and vitality (4 items), social function (2 items), role limitations owing to emotional problems (3 items) and mental health (5 items). The number of questions for each health concept ranges from 2 to 10, and the number of response options per question is either two (yes or no) or six (none, very mild, mild, moderate, severe or very severe). Each of the dimension scores are expressed as a value between 0 and 100, with higher scores representing better health status [22].

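### One rule of mean ± SD and t-tests covers the HRV power variables; log-scale analysis adjusted for baseline would be safer and may recover some power

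*Protocol article*

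**What the plan says.** The Statistical analysis section of the protocol article lists six groups of target variables, one of them being "5) power variables of HRV". It then sets a single rule for the whole list:

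- Description: "All values will be presented as mean ± SD".
- Within groups: a paired t-test "will be used to compare data between the baseline (visit 2) and after the treatment (visit 4) in each group".
- Between groups: "Comparison between the two groups will be performed using independent *t*-test at each time".
- The only alternative: "If there are significant differences between the two groups at the baseline, we will compare the variables using ANCOVA".

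The trigger for that alternative is a baseline imbalance, not the shape of the data. No transformation, geometric mean, rank test or check of distribution is mentioned.

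The Secondary outcome section describes four HRV measures: LF power, HF power, total power and the LF/HF ratio. Total power is called "an indicator of the total amount of variability". Of the ratio it says "The ratio of LF to HF power is commonly interpreted as an indicator of the relative balance". Neither section gives units or a scale for these measures.

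**The concern.** Spectral powers are variance-type quantities. They cannot fall below zero and have no upper limit, so a long right tail is the expected shape, and a ratio of two of them tends to share it. With about 32 women per group, a few large values can dominate the mean and inflate the SD. A t-test on such values is then less sensitive than one on their logarithms, and mean ± SD describes them poorly.

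At stake is the sensitivity and readability of one secondary outcome. The Discussion gives that outcome some weight: it calls this the first trial of autonomic activity after oral red ginseng and says the existing evidence is disputed. A null HRV result from an inefficient test would be harder to interpret.

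The baseline rule adds to this. A visit 2 value is to be compared with visit 4 in every woman, but it enters the between-group comparison only if a significance test at baseline happens to be positive.

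**Working it through.** **Plan's own figure.** The article states no effect, SD or power for HRV, so there is nothing to reproduce on this point. From the Sample size section I take only 32 analysed per group, 1:1 allocation and a two-sided 5% level. (Whether 32 follows from the printed formula is a separate matter. Its inputs give 7.849 × 0.84² × 2 / 0.35² = 90.4, so 91 per group. That does not bear on the comparison below.)

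**Assumptions, not from the documents.** HRV values are log-normal with SD s on the natural-log scale, and treatment multiplies the values. Since s is unknown, I show 0.2 to 1.2.

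**Step 1: effect.** Set the log difference to 0.72 × s. The non-centrality is 0.72 × √(32/2) = 2.88, which gives about 81% power for a t-test on logs at every s. The implied geometric mean ratio is exp(0.72 s).

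**Step 2: power of the two independent t-tests.** 200,000 simulated trials per row, 32 per group:

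| s | geometric mean ratio | power, raw | power, log | loss (points) |
|---|---|---|---|---|
| 0.2 | 1.15 | 80% | 81% | about 1 |
| 0.3 | 1.24 | 79% | 81% | about 2 |
| 0.5 | 1.43 | 76% | 81% | about 5 |
| 0.7 | 1.66 | 72% | 81% | about 9 |
| 1.0 | 2.05 | 62% | 81% | about 19 |
| 1.2 | 2.37 | 55% | 81% | 25 to 26 |

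A second simulation, with the effect set near 80% log-scale power, gave similar losses at 32 and at 40 per group.

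**Step 3: smaller effect.** With a log difference of 0.3 × s, the log test has about 22% power at every s. The raw test has 20%, 18%, 15% and 13% at s = 0.5, 0.7, 1.0 and 1.2. Neither test is then informative.

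**Step 4: validity.** With no effect, the raw-scale tests rejected in 3.5% to 5.2% of simulated trials, so there is no material excess of false positives.

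**Step 5: paired test.** With an assumed within-person correlation of 0.6 on the log scale and 32 women, power on raw versus log values is 70% vs 78% at s = 0.5, 63% vs 77% at 0.7, 55% vs 78% at 0.9 and 43% vs 77% at 1.2. These are within-group comparisons and do not estimate the treatment effect.

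**Step 6: description.** For log-normal data SD/mean = √(exp(s²) − 1). Mean − 2 SD falls below zero once s > √ln 1.25 = 0.47, and mean − SD once s > √ln 2 = 0.83. Power cannot take either value.

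**Step 7: baseline.** Adjusting visit 4 for a baseline value with correlation r multiplies the variance of the between-group comparison by about 1 − r². At the assumed r = 0.6 this is 1 − 0.36 = 0.64; at r = 0 nothing is gained. The simulations above do not include this gain.

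**The case against.** The strongest reply is that the choice of scale for one secondary outcome belongs in a statistical analysis plan, and a condensed article need not give it. The article never says that HRV is analysed on the raw scale, and mean ± SD would suit logged values equally well. This stands in part: raw is the plain reading but is not stated, and an unseen plan may specify logs. It does not dispose of the point, because the article does not stay silent. It fixes one descriptive summary, one set of tests and one conditional baseline rule for all listed variables, HRV included.

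Four further objections limit the size:

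- LF/HF is described in the outcome text, but the analysis list names only power variables, so its testing is inferred. The argument that a raw t-test changes when the ratio is inverted has little force, because the text fixes the direction as LF to HF.
- Exactly log-normal data with a multiplicative effect favour the log test by construction, and the article gives no HRV mean, SD or skewness.
- The simulated effects become large. Ratios of 1.66 to 2.37 at the wider log-SDs have no support in the article.
- HRV is one of several secondary outcomes, the Objectives section does not name autonomic activity, and the trial is described as having a pilot character.

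A reader might infer that the planned t-test is invalid or produces false positives. Step 4 does not support that.

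**Conclusion.** The point holds as a minor one. The stated rule covers the HRV power variables without a transformation and without routine baseline adjustment. Read plainly, it gives a valid test that may be less sensitive than one on logged values, together with a summary that can imply impossible values.

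The size depends on skewness, which the article does not report. Under log-normality, 32 per group and about 81% power on the log scale, the loss runs from negligible (log-SD 0.2 to 0.3) through about 5 points (0.5) and 9 points (0.7) to about 19 and 25 to 26 points (1.0 and 1.2). At small effects both tests have low power.

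A reader might also infer that power for HRV will fall to around 55% or 60%, or that the trial's main conclusion is affected. The documents support neither. The first takes one end of an assumed range combined with a large assumed effect. As to the second, the primary outcome is hand skin temperature, which this point does not touch.

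**What to change.** Pre-specify that LF, HF and total power, and LF/HF if it is to be tested, are analysed as natural logarithms at visit 4. Use ANCOVA with treatment group and the log visit 2 value as covariate, whether or not the groups differ significantly at baseline. Report geometric mean ratios with 95% CI, and describe the raw values by median and quartiles. State whether LF/HF is one of the tested variables. If the full analysis plan already says this, it only needs to be confirmed.

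The cost is a sentence or two in the analysis section and no new data. Results are then read as ratios instead of mean differences, which is a small change in what is estimated. The article reports that recruitment was still under way, so the choice could be fixed before the allocation is unblinded.

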Many studies have suggested that KRG benefits vascular functions. KRG and its ginsenosides had vasodilating action on peripheral vessels and increased the blood flow under cold stress in animal experiments [10]. The ginsenosides isolated from KRG have been reported to cause vasodilation in an endothelium-dependent and nitric oxide- (NO-) mediated manner in a rabbit model [11]. Especially, the ginsenoside Rg3 was proven to inhibit vascular contraction as a consequence of NO production in a rat *in vitro* and *in vivo*[12]. Besides, in humans, KRG improved the vascular endothelial dysfunction in patients with hypertension through increasing synthesis of NO [13]. In addition, according to a randomized, controlled, double-blind trial, KRG was proven to improve arterial stiffness as measured by augmentation index [14]. According to Korean medicine, KRG is considered to have a warm quality and is used as a tonic to invigorate the body and enhance the ‘*Qi*’, which subsequently improves blood flow [15].

The vasodilating action and the warm quality of KRG provide a basis for its potential efficacy on CHHF. However, only one clinical trial has evaluated the effect of KRG on CHHF [16]. In the previous trial, the participants were divided into three groups that received KRG, placebo or nifedipine (a vasodilator). The participants then submerged their hands in cold water and the time until the pain became intolerable was measured. The tolerance time to cold stress significantly increased after administration of KRG compared to the placebo and nifedipine. However, the measurement of the tolerance time to cold stress used in the previous study is a subjective assessment tool.

The aim of the current study is to evaluate the efficacy of KRG on CHHF by using an objective assessment tool, infrared thermography. The hypothesis is that KRG will reduce CHHF more effectively than placebo after eight weeks of administering either KRG or placebo. The outcome measures include changes of skin temperature and the visual analogue scale (VAS) scores of CHHF, the recovery rate (RR) of skin temperature by the cold stress test (CST) of the hands, the distal-dorsal difference (DDD) of the hands, power variables of heart rate variability (HRV), and the 36-item short form health survey (SF-36).

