### Outcomes

#### Primary outcome

The primary outcome is a change of skin temperature in the hands between baseline (visit 2) and after treatment (visit 4). The skin temperature will be obtained by infrared thermography. For the infrared thermography examination, the patient will be asked to avoid hot showers, hot packs, smoking, exercise, acupuncture and stimulants such as caffeine for two hours before the examination. The patient will be acclimatized to room temperature (25 ± 1°C) for 15 minutes and seated comfortably on a chair without physiological or psychological stress. Subsequently, the patient will stand in an anatomical posture. Thermal images of the palm and the upper arm will be obtained to assess cold hypersensitivity in the hands. The difference between the palm and the upper arm, which is related to the severity of cold hypersensitivity in the hands, will then be calculated.

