## Trial status

The study was designed in 2012 and the first participant was randomized on 15 October 2012. Recruitment for this study is ongoing.

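### Within-arm paired t-tests share the P<0.05 threshold with the between-group tests and are not called descriptive, although they cannot test KRG against placebo

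*Protocol article*

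**What the plan says.** The Background section states a comparative hypothesis: "The hypothesis is that KRG will reduce CHHF more effectively than placebo after eight weeks". The Primary outcome section defines the endpoint as the change in hand skin temperature from visit 2 to visit 4.

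The Statistical analysis section opens its efficacy plan with "An efficacy analysis will be performed for both ITT (intention-to-treat) and PP (per-protocol) data set" and lists six groups of target variables, among them the change in skin temperature. It then gives three rules:

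- Within each arm, the paired t-"test will be used to compare data between the baseline (visit 2) and after the treatment (visit 4) in each group".
- Between arms: "Comparison between the two groups will be performed using independent" t-tests, carried out at each time.
- For baseline imbalance: "If there are significant differences between the two groups at the baseline, we will compare the variables using ANCOVA".

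The section closes with one threshold for everything, P-"values <0.05 representing statistical significance". It does not call the paired tests descriptive, and it does not say which comparison carries the efficacy conclusion.

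**The concern.** A change within one arm combines any drug effect with whatever moves both arms. The article gives reasons to think that such a shared movement is possible:

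- Entry requires a palm to upper-arm difference above 0.3 °C, which is the same kind of measure as the primary outcome. Some regression to the mean may follow.
- The VAS and the SF-36 are self-reported, so a placebo response may appear.
- Calendar time may matter in a cold-sensitivity condition: "The study was designed in 2012 and the first participant was randomized on 15 October 2012", and eight weeks of treatment follow.

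A shared change can make one arm significant and the other not, by chance, when the arms do not differ. With the same threshold on both kinds of test and no ranking between them, a report could present that pattern as support for efficacy. A shared change in the unfavourable direction could equally hide a real benefit in the within-arm result.

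**Working it through.** The article gives no figure for this point, so there is none to reproduce. The question is how often, with no treatment effect, the KRG arm improves significantly while the placebo arm does not.

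**Inputs from the article.** Evaluable n = 32 per arm (Sample size section); 40 per arm if nobody drops out (80 in total, allocated 1:1); two-sided 5% threshold. The article's own formula with 0.35 and 0.84 does not return 32: (1.960 + 0.842)² × 0.84² × 2 / 0.35² ≈ 90.4, so 91. That is a separate matter. Here 32 is used only as the planned number.

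**Assumed inputs.** Shared change *s*, in SDs of a single measurement, from 0 to 0.6; correlation *r* between visits, 0.5 or 0.7.

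**Formulas.**

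1. Shared change in SDs of the change: d = s / √(2(1 − r)).
2. Noncentrality of the paired t: δ = d√n, with n − 1 = 31 degrees of freedom and critical value 2.040.
3. p = probability that one arm shows a significant improvement (upper tail of the noncentral t).
4. The arms are independent, so P(KRG only) = p(1 − p). This cannot exceed 0.25, which it reaches at p = 0.5.

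**Worked case, s = 0.3.**

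- r = 0.5: d = 0.3/1 = 0.300; δ = 0.300 × 5.657 = 1.697; p = 0.376; 0.376 × 0.624 = 0.235.
- r = 0.7: d = 0.3/0.775 = 0.387; δ = 2.191; p = 0.565; 0.565 × 0.435 = 0.246.

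**Results, 32 per arm, no treatment effect, per endpoint.**

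| Shared change (SD) | P(KRG only), r = 0.5 | P(KRG only), r = 0.7 |
|---|---|---|
| 0 | 2.4% | 2.4% |
| 0.1 | 7.3% | 9.4% |
| 0.2 | 15.6% | 20.7% |
| 0.3 | 23.5% | 24.6% |
| 0.5 | 17.0% | 5.4% |
| 0.6 | 8.4% | 1.1% |

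The rate falls again for large shifts because both arms then become significant. With 40 per arm the 0.3 SD row is 24.8% and 22.2%.

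**Comparison.** A two-sided 5% between-arm test errs in KRG's favour 2.5% of the time. In simulations of 100,000 trials per scenario (d = 0.3 and 0.35; 32 and 40 per arm), a between-arm t-test on the change rejected in 4.8–5.0%. Among the simulated trials that showed the KRG-only pattern, that test was significant in only 9–10%.

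**The case against.** The strongest reply is that the plan already contains the right kind of test. The sentence after the paired test provides a between-group t-test, and with randomized arms a visit 4 comparison is protected from season, placebo response and regression to the mean, which both arms share. This stands.

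A reader might infer that the trial will judge efficacy by setting one arm's P-value against the other's, or that the paired test is the only one applied to the change. The article supports neither. It never says that conclusions rest on the paired tests. Its list of target variables includes the change itself, so the between-group test may be meant for the change as well, although the wording about each time leaves this unclear.

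The size is also open to challenge. The 0.3 SD row lies close to the 25% ceiling, and nothing in the article fixes the shift. The sources of drift may be weak:

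- **Regression to the mean.** The Discussion gives the 0.3 °C cut-off a sensitivity of 94.0%. If measurements are roughly normal and the population similar, removing the lowest 6% raises the mean by about 0.119/0.94 = 0.13 SD. The expected return is then (1 − r) × 0.13, or 0.04–0.06 SD, for which the KRG-only rate is about 4–5%. Selection on complaints could add to this, but the article does not quantify it.
- **Season.** Imaging follows 15 minutes at 25 ± 1 °C, and a palm to upper-arm difference is calculated. Recruitment was still open, so one common seasonal direction is not established.

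These points limit the size. They do not give the within-arm P-values a comparative meaning.

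It could also be said that ranking the tests is left to a fuller document. The common threshold and the conditional ANCOVA are, however, stated here and can be judged as stated.

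**Conclusion.** The point holds as a matter of how the tests are framed. It does not show that the planned between-group analysis is invalid. The paired tests stand beside the between-group tests at the same P<0.05 and are not labelled descriptive, while the hypothesis is comparative.

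With no treatment effect and 32 per arm, the misleading KRG-only pattern has a chance per endpoint from about 2.4% (no shared change) up to the 25% ceiling (near 0.3 SD), and falls again for larger shifts. The whole range rests on an assumed shift and an assumed visit correlation of 0.5–0.7. It measures how often the pattern would appear, not the error rate of any decision rule in the article.

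**What to change.** In the Statistical analysis section:

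- Report the within-arm mean change with SD, or with a confidence interval, as description and without P-values.
- State that efficacy conclusions rest on the between-group difference at visit 4, adjusted for the visit 2 value, with a 95% CI.
- Use that ANCOVA in all cases, not only after a significant baseline difference. The choice of model then no longer depends on a baseline test, and the uncertainty about what is compared at each time goes away.

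The adjustment should also gain precision. Relative to a plain visit 4 t-test, the large-sample variance is multiplied by 1 − r²: 0.75 at r = 0.5 and 0.51 at r = 0.7, under the same assumed correlations.

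The cost is wording only. It needs no new data, visits or participants. The one thing lost is the within-arm P-values in the report, which the hypothesis does not need.

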### Sample size

This trial has a pilot characteristic to evaluate the efficacy of KRG on CHHF by using infrared thermography. Although there was no previous study that is the same in design, we calculated the sample size on the basis of a study that used similar variables. The previous study measured the tolerance time to cold stress to assess the efficacy of KRG on CHHF using a two-sided test, yielding a 5% significance level [16]. The formula for estimating the sample size is as follows:

$$n_{t}=n_{c}=\left\{{\left(Z_{\alpha /2}+Z_{\beta }\right)}^{2}\sigma^{2}\left(\lambda +1\right)/\lambda \right\}/{\left(\mu_{t}-\mu_{c}\right)}^{2}$$

In the previous study, the tolerance time to cold stress prolonged 0.35 minute in the KRG group compared with the control group (μ_t_-μ_c_), and a mean standard deviation (σ) was 0.84. In our study, the ratio (λ) of KRG to placebo is 1:1. With an 80% power (1-β) and a 5% significance level (α), assuming μ_t_-μ_c_ = 0.35 and σ = 0.84, a sample size of *n*_
*t*
_ *= n*_
*c*
_ = 32 patients per group is needed (*n*_
*t*
_, number of patients in KRG group; *n*_
*c*
_, number of patients in placebo group). Anticipating a drop-out rate of approximately 20%, the total sample size should be more than 80 women.

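### Baseline adjustment is used only if a baseline significance test rejects, so the trial data choose the primary model and power is usually lost

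*Protocol article*

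**What the plan says.** All the relevant analysis text is in the Statistical analysis section of the protocol article.

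- Default between-group comparison: "Comparison between the two groups will be performed using independent *t*-test at each time".
- Exception: "If there are significant differences between the two groups at the baseline, we will compare the variables using ANCOVA".
- Baseline testing: "Baseline characteristics such as age and body mass index (BMI) between the two groups will be compared using independent *t*-test or chi square test".
- Threshold: "with *P*- values <0.05 representing statistical significance".

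The Primary outcome section defines the endpoint as the change in hand skin temperature from visit 2 to visit 4, and the list of target variables under Statistical analysis also names a change of skin temperature. The sentence on the default t-test speaks instead of each time point, which reads as raw values at each visit. The Randomization section gives 1:1 allocation without stratification. The article nowhere states a baseline-adjusted analysis that applies whatever the baseline test shows.

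**The concern.** Under randomisation every baseline difference is due to chance, so a baseline significance test says nothing about whether adjustment is worthwhile. What decides that is how strongly the visit 2 value predicts the visit 4 value. The plan therefore uses the wrong criterion to choose its model, and the choice is made by the trial's own data.

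Two things are at stake. The first is efficiency: in most trials the analysis would be an unadjusted t-test although a more precise analysis of the same data is available. The second is a fixed primary analysis: from the text, the primary comparison could be a t-test on visit 4 values, a t-test on change, or ANCOVA. The first two readings differ considerably in power.

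**Working it through.** **Inputs from the document.** The planned analysable size is stated as "32 patients per group is needed", and the threshold is 0.05. It is taken as two-sided because the sample size formula uses Z for α/2.

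**The plan's own figure.** The Sample size section states: "With an 80% power (1-β) and a 5% significance level (α), assuming μ_t_-μ_c_ = 0.35 and σ = 0.84". Its formula with λ = 1 gives (1.960 + 0.842)² × 0.84² × 2 / 0.35² = 90.4, so 91 per group and not 32. That is a separate defect. Here 32 is used only because it is the number per group that the plan expects to analyse.

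**Assumptions not in the document.** The correlation ρ between visit 2 and visit 4 values is shown over a range. SDs are equal at both visits and the data are normal. The trigger is a t-test on the baseline of the same variable. The effect is 0.6 SD, or alternatively 0.35/0.84 = 0.42 SD, which in the document concerns cold tolerance time and not skin temperature.

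**Step 1: how often the trigger fires.** A 5% test of a true null rejects in 5% of trials. The simulated rate was 4.9–5.1%.

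**Step 2: variance of the treatment estimate, relative to a t-test on visit 4 values.**

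- Visit 4 t-test: 1
- Change-score t-test: 2(1 − ρ)
- ANCOVA: 1 − ρ²

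The ratio of ANCOVA to the change-score test is (1 − ρ²)/[2(1 − ρ)] = (1 + ρ)/2. For any ρ strictly between 0 and 1, ANCOVA therefore has the smallest large-sample variance. At ρ = 0.5 the three values are 1, 1 and 0.75. With an effect that needs 32 per group under either t-test for 80% power (0.70 SD), ANCOVA needs 32 × 0.75 = 24.

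**Step 3: power of the rule as written.** The simulated rule tests baseline at 0.05, uses ANCOVA if that rejects and otherwise uses the t-test, with 32 per group. For an effect of 0.6 SD:

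| ρ | Rule, visit 4 values | Rule, change | ANCOVA always |
|---|---|---|---|
| 0.3 | 65% | 52% | 69% |
| 0.5 | 66% | 66% | 77% |
| 0.7 | 67% | 87% | 91% |

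Repeat runs moved these figures by about one percentage point. The loss against ANCOVA is 4, 11 and 24 points on the visit 4 reading, and 17, 11 and 4 points on the change reading. With 0.42 SD and ρ = 0.5, the rule gives about 38% on either reading against 47%.

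**Step 4: overall type I error of the rule** (100,000 simulated trials per setting):

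| ρ | Rule, visit 4 values | Rule, change |
|---|---|---|
| 0.3 | 4.8% | 4.1% |
| 0.5 | 4.4% | 4.5% |
| 0.7 | 3.7% | 4.6% |
| 0.8 | 3.1% | 4.7% |

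ANCOVA always gave about 5% throughout. The rule falls below 5% because it switches to ANCOVA in the trials with the largest imbalance, where an unadjusted test would reject too often, and leaves the other trials as they are.

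**The case against.** The strongest reply is that the endpoint is a change. If the t-test is on change scores, every patient's baseline is subtracted, so a reader who infers that the plan ignores baseline goes too far. That stands: on this reading baseline enters with a fixed slope of 1, and at ρ = 0.7 the rule loses only about 4 points. What remains is that the text does not settle the reading, and that at low ρ the change score is the worse choice.

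A reader might also infer that the rule inflates false positives. The documents do not support this.

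- The rule as written is conservative overall (step 4).
- Taking the best of the three tests would give about 9–10%, but the plan nowhere allows a choice by smallest p-value. It states a default and a trigger, and has an independent statistician work blinded.
- With a baseline z of 1.9, just short of the trigger, the conditional false-positive rate of a visit 4 t-test is about 12% (ρ = 0.5) to 19% (ρ = 0.7). This is one selected case on one reading. A |z| between 1.8 and 1.96 occurs in about 2% of trials, and such cases are offset elsewhere.

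Nor can a material loss be asserted for every outcome, since no correlations are given for any of them. The Sample size section calls the trial pilot in character, and at 0.42 SD and ρ = 0.5 power is below 50% under either analysis, which is a matter of sample size. These points bear on severity. They do not remove the stated trigger, and blinding the statistician does not stop the baseline test from choosing the model. A statistical analysis plan that is not shown could settle the t-test variable, but the conditional rule is stated in the article itself.

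**Conclusion.** The concern holds as a matter of efficiency and of an unfixed primary model. Baseline adjustment depends on a chance event of about 5% per variable, so about 95% of trials would forgo ANCOVA. At an assumed 0.6 SD and 32 per group, the cost ranges from about 4 to 24 power points, depending on ρ and on which variable the t-test uses; at ρ = 0.5 it is about 11 points on either reading. The loss is small for visit 4 values at low correlation and for change scores at high correlation. The effect sizes and correlations are assumptions. That ANCOVA is at least as precise in large samples does not depend on the particular value of ρ. The overall test remains valid, if conservative. Severity: should-fix.

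**What to change.** Delete the sentence that makes ANCOVA depend on a significant baseline difference, and replace the default t-test for the between-group comparison. Suggested wording: *The visit 4 value will be compared between groups by ANCOVA with treatment as factor and the visit 2 value of the same variable as covariate, whatever the observed baseline difference. The adjusted mean difference and its 95% confidence interval will be reported.* Apply it to the primary outcome and to each continuous secondary outcome. This also settles whether visit 4 values or change scores are tested, because with the visit 2 value as covariate both give the same treatment estimate. The baseline table can stay but must not decide the model.

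The cost is wording only. Visit 2 values are already collected, and the article already names ANCOVA and the software. Recruitment was ongoing according to the Trial status section, so the change can be made and dated before unblinding.
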